## 5.2 Randomisation and Blinding

A total of 60 eligible participants will be randomly assigned at a 1:1 ratio to one of the two groups at the baseline visit. The equal randomisation will be conducted by the staff at the Key Unit of Methodology in Clinical Research (KUMCR) of the GPHCM who is independent of the trial investigators. Only the person has access to the results of randomised allocation. The random allocation sequence will be generated through the blocked randomisation method using the SAS software (version 9.2, SAS Institute, Inc., Cary, NC, USA). Then the randomisation code corresponding to the trial medications will be released by the Interactive Web Response System for Chinese Medicine Trials that is a verified online randomisation facility established by the KUMCR (<http://59.42.21.236:8088/randomisation/portal/portalLogin>). Therefore, the allocation concealment will be ensured.

The participants, trial investigators, outcome assessors, the statistician, and the pharmacist who dispense medications will be blinded to the allocation. The randomisation code can be broken if the appropriate management of the patient in medical emergencies necessitates knowledge of the treatment randomisation. It should be applied by the trial investigator through the online randomisation system and then the principal investigator will be notified to approve of breaking the code. Therefore, the type of trial medications (CHM or placebo) will be identified. In addition, the reason, date, and result of breaking the randomisation code will be recorded in the patient's case report form. Any condition resulting in an unblinding event will report to the ethics committee of the GPHCM. Breaking the randomisation code under medical emergencies should not spread to ensure the clinical trial continues. If a patient's treatment is unblinded by the investigator, the patient will be withdrawn from the study.

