#### 5.3.5 Trial duration

The trial period is 20 weeks, including an 8-week treatment phase and a 12-week follow-up phase.

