##### 5.4.1.2 Outcome measures and visits

- PASI, BSA, sPGA and itch VAS: Participants will be evaluated these measures at week 0, 2, 4, 6, 8, 12, 16 and 20
- DLQI and Skindex-16: Evaluate these measures at week 0, 8, and 20
- 11-point ordinal scale: Evaluate it at week 8 and 20
- Blinding credibility: Evaluate it at week 8 and 20
- Chemical examinations: Evaluate electrocardiograms at the baseline, and collect blood (two 4 ml-EDTA tubes and two drying tubes) and urine (one 10 ml-urine tube) at week 0, 8 and 20
- Photos taken for representative skin lesions: Conduct it at each visit
- Concomitant medication, and AEs: Record it during the whole trial phase

- Dispense and collect trial drugs: Dispense trial drugs at week 0, 2, 4, and 6; collect trial drugs at week 2, 4, 6 and 8
- Dispense and collect home diary record sheet: Dispense it at week 0, 2, 4, 6, 8, 12, and 16; collect it at week 2, 4, 6, 8, 12, 16 and 20

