## 5.5 Termination and withdrawal

If participants are diagnosed with other type psoriasis (erythrodermic psoriasis, psoriatic arthritis, or pustular psoriasis) or suffer from serious adverse events during the trial, the study will be terminated. In addition, participants have the right to withdraw from the study at any time for any reason. Trial investigators can receive feedback on trial medications from these participants and ask them to complete the relevant examinations, which will help the researcher to collect data and benefit the care of participants' health.

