### 5.7.2 Other types of psoriasis

If participants in the trial are diagnosed with other type psoriasis (erythrodermic psoriasis, psoriatic arthritis, or pustular psoriasis) by researchers, the study will be terminated. They will be treated according to psoriasis clinical guidelines.

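### Unblinding, a serious adverse event or a new psoriasis type ends a participant's follow-up as well as trial treatment, so a little safety and outcome data may be lost needlessly

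*Protocol*

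**What the plan says.** Three rules in the protocol remove a participant after an event.

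- **Unblinding (section 5.2):** "If a patient's treatment is unblinded by the investigator, the patient will be withdrawn from the study". The same paragraph says that an emergency code break "should not spread to ensure the clinical trial continues".
- **Serious adverse event or another psoriasis type (section 5.5):** participants who develop erythrodermic or pustular disease or psoriatic arthritis, "or suffer from serious adverse events during the trial, the study will be terminated".
- **Another psoriasis type (section 5.7.2):** on such a diagnosis "by researchers, the study will be terminated". The next sentence reads "They will be treated according to psoriasis clinical guidelines".

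On data after an exit, section 5.5 says only this, directly after the sentence on voluntary withdrawal: "Trial investigators can receive feedback on trial medications from these participants and ask them to complete the relevant examinations".

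On timing, section 5.3.5 states: "The trial period is 20 weeks, including an 8-week treatment phase and a 12-week follow-up phase". On event capture, section 5.4.1.2 states: "Concomitant medication, and AEs: Record it during the whole trial phase".

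**The concern.** Stopping trial treatment and stopping observation are separate decisions, and none of the three rules separates them. An unblinded participant, or one with a serious event, can still attend for blood tests, vital signs and a skin assessment. Nothing in the protocol says that those visits go on.

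The rules also apply in weeks 8 to 20. No trial treatment is given then, so follow-up is the only thing left for them to stop.

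The exits happen for safety- or disease-related reasons, and safety and acceptability are among the pilot's objectives (section 3.2). The people whose later safety data would be most useful are therefore the ones whose scheduled visits end. Their later PASI values would be imputed under section 5.9.2 although they could have been observed. That holds only if they are in the ITT set, which requires at least one dose and data from at least one visit.

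**Working it through.** **What the rules end.** The three rules and the post-exit sentence, side by side:

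| Section | Trigger | What ends | Visits kept |
|---|---|---|---|
| 5.2 | Code broken by the investigator | Participation in the study | None stated |
| 5.5 | Serious adverse event, or another psoriasis type | The study, read as that person's participation | None stated |
| 5.7.2 | Another psoriasis type | As above, then guideline treatment | None stated |
| 5.5, post-exit sentence | Voluntary withdrawal, possibly also removal by rule | Not applicable | Optional examinations, none named, no visit named |

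**Data at risk for one participant.** From Table 1, post-baseline PASI visits are at weeks 2, 4, 6, 8, 12, 16 and 20, which is 7. Post-baseline blood and urine tests, vital signs, physical examination and the acceptability rating are each at weeks 8 and 20, which is 2. The primary time points are weeks 8 and 20 (section 5.6.2.1).

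| Item | Exit just after week 4 | Exit just after week 8 |
|---|---|---|
| PASI visits | 5 of 7 | 3 of 7 |
| Primary time points | 2 of 2 | 1 of 2 |
| Blood and urine tests | 2 of 2 | 1 of 2 |
| Vital signs and physical examination | 2 of 2 | 1 of 2 |
| Acceptability ratings | 2 of 2 | 1 of 2 |

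Two items are left out because continued visits would not usefully recover them: blinding ratings after a code break, and week-20 relapse status after a switch to guideline therapy.

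The treatment-free share of the trial is 12/20 = 60% of the weeks.

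**How many participants.** The protocol gives no event rates. At an assumed serious-event risk of 0.5% to 2%, the expected number is 60 × 0.005 = 0.3 to 60 × 0.02 = 1.2, or 0.15 to 0.6 per arm of 30. No rate can be offered for unblinding or a new psoriasis type. If 1 to 3 of 60 were affected by any of the three triggers (also an assumption), that is 1.7% to 5.0% of the sample.

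**Precision.** Losing 1 to 3 of 60 inflates a standard error by √(60/59) = 1.008 to √(60/57) = 1.026, that is by 0.8% to 2.6%.

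**Effect on the efficacy estimate.** Take one exit in one arm of 30, with the imputed PASI wrong by an assumed 1 to 3 points.

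- Shift in that arm's mean: 1/30 = 0.03 to 3/30 = 0.10 PASI points.
- Standard error of the arm difference: SD × √(2/30). An assumed SD of 2 gives 0.516; an assumed SD of 4 gives 1.033.
- Shift relative to that standard error: 0.033/1.033 = 0.03 to 0.10/0.516 = 0.19.

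**The case against.** The case for leaving the text alone has real force.

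- **Size.** About one participant is affected, and 1 to 3 exits are small beside the 15% loss to follow-up that section 5.9.1 allows (0.15 × 60 = 9). This stands, and it is why the point is minor.
- **Existing cover.** Section 5.5 is headed for both termination and withdrawal, so its sentence on examinations can be read as covering participants removed by rule. That reading is fair but not certain, given where the sentence sits. On either reading the examinations are optional and unspecified, so some data may be rescued but none is assured.
- **Protecting the blind.** PASI is assessor-rated in a double-blind trial, so ending participation after an emergency code break is defensible. That is a reason to mark or set aside later efficacy scores. It is not a reason to give up laboratory tests and vital signs.
- **Quality of the recovered scores.** PASI obtained after unblinding or under guideline therapy is not clean. This stands, and such scores need flagging.
- **Matters for the SAP.** How those scores enter the main estimate can be left to the SAP. Whether the participant is seen at all is a conduct rule that the protocol itself sets, and no analysis plan can restore visits that were not made.

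A reader might infer that one serious adverse event closes the whole trial. The context does not support that: section 5.2 wants the trial to carry on after a code break, and section 5.7.2 goes on to the treatment of the affected patients. The phrase is a wording fault.

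A reader might also infer that the triggering event goes unrecorded. It does not. Adverse events are recorded throughout (5.4.1.2), serious ones are reported within 24 hours (5.6.3), and the reason, date and result of a code break go into the case report form (5.2).

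**Conclusion.** The point holds as a minor, cheap improvement. As written, the three rules end observation as well as treatment, and the only post-exit data collection is optional and unscheduled. The main loss is later safety follow-up, with some acceptability and PASI data, in a handful of participants at most.

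The documents do not support a claim of material bias in the efficacy result. A shift of 0.03 to 0.19 standard errors per exit is very small, and a serious event unrelated to psoriasis need not be informative for efficacy at all. The visit counts come from Table 1. The serious-event risk, the number of exits, the imputation error and the SD are all assumptions, because the protocol gives none of them.

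**What to change.** In sections 5.5 and 5.7.2, replace the clause that ends the study with one that stops the individual participant's trial treatment. In section 5.2, change withdrawal from the study to withdrawal from trial treatment. In all three, state that the scheduled safety and outcome visits continue to week 20 unless the participant withdraws consent, and that scores obtained after unblinding or a switch of therapy are flagged.

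The cost is wording in three sections. The visits are already in Table 1 and the sample size stays at 60. The downside is that a few efficacy scores will come from participants who are unblinded or receiving other therapy; their place in the main estimate can be set in the SAP.

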## 5.3 Intervention and control

### 5.3.1 FZHFZY formula

FZHFZY includes seven herbs: *Cynanchum paniculatum* (Bge.) Kitag. (*xu chang qing*), *Dictamnus dasycarpus* Turcz. (*bai xian pi*), *Cnidium monnieri* (L.) Cuss. (*she chuang zi*), *Smilax glabra* Roxb. (*tu fu ling*), *Rehmannia glutinosa* Libosch. (*shu di huang*), *Angelica sinensis* (Oliv.) Diels. (*dang gui*) and *Punica granatum* L. (*shi liu pi*) [30, 31], the dosage ratio of seven herbs is 3:3:2:3:3:2:3 respectively. FZHFZY will be produced into granules by Tianjiang Pharmaceutical Co., Ltd. (Jiangyin, Jiangsu Province, China), a manufacturer holding a Chinese Good Manufacturing Practice certificate. These herbs will be mixed, boiled, filtered and pressure spray-dried to form granules. Then will be packaged in a single-dose sachet (11.0 cm× 15.5 cm), weighing 100 g each. The administration instructions and precautions of the intervention are listed as follows.

#### 5.3.1.1 Administration instructions

One packaged of FZHFZY granules will dissolve in warm water at 35°C to 38°C. The amount of

water will be adjusted according to the size of the bathtub and the location of the skin lesion. Participants will be instructed to adjust their bathing position to ensure the psoriasis lesions will be soaked by the liquid. The height of liquid should not exceed the chest when a patient is in a semi-recumbent or sitting position if a whole-body bath is required. Where a whole-body bath is not needed, patients may reduce the amount CHM/placebo granule and water according to doctor's instruction. The bathing duration is between 15 and 20 minutes once a day for eight weeks at home.

#### 5.3.1.2 Administration precautions

- The external application as whole-body bath or topical bath, as well as the amount of water and dosage will depend on the size of the bathtub and the location of skin lesion, as well as the acceptability of patients.
- Take a bath after cleansing the skin. The right liquid temperature is between 35°C to 38°C according to individual preference.
- The height of liquid should not exceed the chest when a patient is in a semi-recumbent or sitting position if a whole-body bath is required.
- Pay attention to ventilation when bathing the whole body, it is not suitable for closed space.
- Avoid getting cold and drinking alcohol, prevent fall injury before and after bathing.
- Please suspend the bath with cold and fever.
- Please suspend the bath for women during menstruation.
- If patients have observed any allergic reaction, please stop the bath therapy and contact the researcher immediately for further instruction.
- If there is any skin damage caused by injuries, please stop the bath therapy and contact the researcher immediately for further instruction.
- If patients feel unwell during the bath, e.g. skin irritation, chest tightness and shortness of breath, please discontinue it.

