### 5.6.3 Safety outcomes

Safety assessments will consist of incidence and frequency of adverse events (AEs) and serious AEs during the trial period, the evaluation of application site tolerability, clinical laboratory parameters (complete blood count, urinalysis, hepatic and renal functions), vital signs (heart rate, body temperature, respiratory rate and blood pressure), and physical examinations at week 0, week 8 and week 20. Each patient with an adverse event will be counted only once for each Medical Dictionary for Regulatory Activities (MedDRA), version 22.0, preferred term [52]. The severity of AEs will be based on the Common Terminology Criteria for Adverse Events, version 5.0 [53]. The WHO-UMC system will be used for standardised case causality assessment [54]. Serious AEs should be reported to the GPHCM Ethics administration within 24 hours and be recorded in the serious AEs form.

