## 5.7 Pre-assessment and disposal plan of relevant risks

### 5.7.1 Adverse reaction of CHM bath therapy

The common adverse reaction of CHM bath therapy is skin irritation (e.g. skin erythema, itching), chest tightness and shortness of breath. These symptoms may disappear if participants stop the bathing immediately. If participants suffer from any unexpected condition no matter whether it is related to the trial medications or not, they can contact the researcher immediately for further suggestions.

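### For chest tightness or shortness of breath in a home bath, no protocol rule clearly requires contact or assessment before the next daily bath

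*Protocol*

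**What the plan says.** Protocol 5.3.1.1 sets the exposure: "The bathing duration is between 15 and 20 minutes once a day for eight weeks at home".

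Protocol 5.3.1.2 ends with three bullets on what to do when something goes wrong:

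- Allergic reaction: "If patients have observed any allergic reaction, please stop the bath therapy and contact the researcher immediately for further instruction".
- Skin injury: "If there is any skin damage caused by injuries, please stop the bath therapy and contact the researcher immediately for further instruction".
- Feeling unwell: "If patients feel unwell during the bath, e.g. skin irritation, chest tightness and shortness of breath, please discontinue it".

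Protocol 5.7.1 returns to the symptoms in the third bullet: "The common adverse reaction of CHM bath therapy is skin irritation (e.g. skin erythema, itching), chest tightness and shortness of breath". It adds: "These symptoms may disappear if participants stop the bathing immediately". On contact it says: "If participants suffer from any unexpected condition no matter whether it is related to the trial medications or not, they can contact the researcher".

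For adverse events generally, 5.4.1.2 has them recorded throughout the trial, and 5.6.3 sets a deadline for serious ones only: "Serious AEs should be reported to the GPHCM Ethics administration within 24 hours and be recorded in the serious AEs form". Section 5.5 acts on a serious adverse event, on a change to another type of psoriasis, or on the participant's own wish to withdraw.

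**The concern.** The first two bullets ask for two things: stop the therapy, and call at once. The third asks for one, and it is the bullet that covers chest tightness and shortness of breath. On the page, a possible heart or lung symptom gets a weaker response than a skin injury.

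Section 5.7.1 does not repair this. Its verb is permissive, and its trigger is an unexpected condition, two sentences after these symptoms are described as common. A participant could reasonably conclude that no call is needed.

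The baths are unsupervised and daily, so the participant may decide alone whether to bathe again the next day. The exclusion in 5.1.2 removes only uncontrolled or severe cardiovascular and respiratory disease, so people with controlled or milder disease can be enrolled. Protocol section 2 states that the formula's safety has not yet been tested in a rigorous randomised trial. What is at stake is participant safety, not any estimate or test.

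**Working it through.** The plan gives no figure on this point to reproduce. The check compares the instructions and then works out the timing.

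**1. Response required, by event (5.3.1.2 and 5.7.1)**

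| Event | Stop | Contact | Condition for restarting |
|---|---|---|---|
| Allergic reaction | the therapy | immediate, required | further instruction |
| Skin injury | the therapy | immediate, required | further instruction |
| Chest tightness, shortness of breath, skin irritation | *it* | optional, and only if *unexpected* | none stated |

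**2. What *it* refers to.** The nearest noun is the bath being taken. The neighbouring bullets name the therapy when they mean the course, and 5.7.1 speaks of symptoms fading once bathing stops. These point to the single bath. Against that, two other bullets in the list ask participants to suspend the bath during a cold or fever and during menstruation, where *the bath* means bathing over several days. The single-bath reading is the more natural one, but it is not certain.

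**3. Timing if *it* means that bath**

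- Planned baths: 8 weeks × 7 days = 56.
- Visits during treatment (5.4): weeks 0, 2, 4, 6 and 8, so the interval is 2 × 7 = 14 days.
- Next exposure after a symptom: about 1 day.
- Next scheduled assessment: up to 14 days.

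**4. Whether another rule closes the gap**

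- *Allergy bullet:* applies if the participant recognises the symptom as allergic.
- *Serious adverse event rules (5.5, 5.6.3):* apply only if the event is serious.
- *Adverse event recording and home diary (5.4.1, 5.4.1.2):* diary sheets are collected at visits, so they do not prompt a review before the next bath.
- *Baseline ECG and the 5.1.2 exclusions:* reduce risk at entry but do not govern what happens after a symptom.
- *Ventilation and chest-height advice (5.3.1.2):* lowers the chance of a symptom but does not deal with one that has occurred.

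What remains is a non-serious episode of chest tightness or breathlessness that the participant does not take to be allergic. No rule in the protocol requires contact or assessment for it before the next bath.

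**The case against.** The best counter-argument is that *discontinue it* may mean stopping the therapy. If so, no bath follows the next day and the harm described does not arise. The two *suspend the bath* bullets give this some support, so the wording should be called ambiguous. It does not remove the point: on that reading the participant stops treatment, even for mild skin irritation, with no duty to tell anyone. Either way the sentence needs rewording.

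Second, *unexpected* in 5.7.1 may carry its everyday sense of something untoward, which would include these symptoms. That is plausible, but contact is still only permitted.

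Third, consent pages are not in the text reviewed, and the diary sheet and standard operating procedures are not shown. They may tell participants to call. The point is therefore about the protocol's own instructions; it does not show what participants are actually told.

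Three stronger readings are tempting, and the document does not support them:

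- A reader might infer up to about 13 further symptomatic baths before the next visit (14-day interval, symptom just after a visit). The text does not clearly forbid this, but the count assumes that the symptom recurs daily and that the participant never calls.
- A reader might want a number of affected participants. The protocol gives no frequency, so any such number would be invented.
- A reader might extend mandatory stop-and-contact to persistent or recurrent skin irritation. The argument here concerns heart and lung symptoms. Itch and redness also come from psoriasis itself, so that rule could interrupt dosing for the disease under treatment.

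**Conclusion.** The point holds as a wording gap that bears on participant safety. For chest tightness or shortness of breath that is neither recognised as allergic nor serious, the protocol requires no contact or assessment before the next daily bath, although it does so for allergic reaction and skin injury.

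Its size can be stated only per episode: about 1 day to the next bath against up to 14 days to the next scheduled visit. This rests on reading *discontinue it* as that bath, which is the more natural reading but not the only one. How many of the 60 participants would be affected cannot be derived from the document. No endpoint, sample size or analysis is touched. The change is worth making because it is small and largely reuses a rule the protocol already has.

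**What to change.** In 5.3.1.2, split the last bullet in two:

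- *If chest tightness or shortness of breath occurs, stop the bath therapy, contact the researcher immediately and do not resume until advised.*
- *If skin irritation occurs, end that bath and record it in the diary.*

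In 5.7.1, change *can contact* to *must contact* for chest tightness and shortness of breath only, and leave contact optional for other unexpected conditions. Section 5.3.2 already makes the instructions identical for formula and placebo, so the change applies equally to both arms.

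The cost is a few extra calls and a few missed baths for each affected participant. Each missed bath is 1/56 = 1.8% of the planned course. If a pause lasts 1 to 3 days (an assumption), the loss is 1/56 = 1.8% to 3/56 = 5.4% of that participant's baths.
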